### Study Assessment Procedures

#### Overview

Patient-reported outcomes (Table 1) will be completed on the web using Research Electronic Data Capture (REDCap; Vanderbilt University) [111]. Participants will also have the option to complete these study assessments on paper or over the telephone with research staff. Study assessment materials will be available in English or Spanish. Patient-reported outcome measures for anxiety, comorbid symptoms, and quality of life have been validated in Spanish [112-117]. Where needed, Spanish translation of other assessments took place in standard forward and reverse translation.

**Table 1 table1:** Summary of patient-reported outcomes.

Primary or secondary	Name of outcome	Validated instrument	Time points (weeks)
Primary	Anxiety	HADS^a^	0, 4, 8, 16, and 26
Secondary	Depression	HADS	0, 4, 8, 16, and 26
Secondary	Fatigue	BFI^b^	0, 4, 8, 16, and 26
Secondary	Insomnia	ISI^c^	0, 4, 8, 16, and 26
Secondary	Pain	BPI^d^	0, 4, 8, 16, and 26
Secondary	Cognitive dysfunction	FACT-Cog^e^	0, 4, 8, 16, and 26
Secondary	Quality of life	PROMIS–Global Health^f^	0, 4, 8, 16, and 26
Secondary	Treatment expectancy	METE^g^	0 and 8
Secondary	Treatment preference	Treatment preference Scale	0 and 8
Secondary	Music reward	BMRQ^h^	0
Secondary	Mental health stigma	SSRPH^i^	0
Secondary	Generalized anxiety disorder	GAD-7^j^	0

^a^HADS: Hospital Anxiety and Depression Scale.

^b^BFI: Brief Fatigue Inventory.

^c^ISI: Insomnia Severity Index.

^d^BPI: Brief Pain Inventory.

^e^FACT-Cog: Functional Assessment of Cancer Therapy–Cognitive Function.

^f^PROMIS–Global Health: Patient-Reported Outcomes Measurement Information System–Global Health.

^g^METE: Mao Expectancy of Treatment Effects.

^h^BMRQ: Barcelona Music Reward Questionnaire.

^i^SSRPH: Stigma Scale for Receiving Psychological Help.

^j^GAD-7: Generalized Anxiety Disorder 7-Item Scale.

#### Anxiety

The primary outcome is severity of anxiety symptoms, as assessed using the HADS anxiety subscale. The reliability, validity, and factor structure of this 7-item subscale has been established in patients with cancer with a Cronbach α of .83 [118,119]. A score of ≥8 indicates the presence of anxiety symptoms. Research has identified a minimal clinically important difference (MCID) of 1.7 points [120]. The HADS anxiety subscale will be administered at baseline and at weeks 4, 8, 16, and 26.

#### Comorbid Symptoms and Quality of Life

Given that anxiety is strongly associated with depressed mood [11-13], fatigue [14-17], insomnia [10], pain [121], and cognitive dysfunction [122], these comorbid symptoms will be assessed using validated instruments. Depressive symptoms will be assessed using the HADS depression subscale (Cronbach α=.79) [118,119]. Fatigue will be assessed using the Brief Fatigue Inventory (BFI), a 9-item scale that has been validated in cancer populations with a Cronbach α of .96 [123]. Insomnia symptoms will be assessed using the Insomnia Severity Index [124], a 7-item instrument validated in cancer populations with a Cronbach α of .90 [125]. Pain severity and pain-related interference will be assessed using the Brief Pain Inventory (BPI). The BPI has been demonstrated to be a reliable, valid, and responsive measure with a Cronbach α of .77 to .91 [126]. Cognitive difficulties will be assessed using the Functional Assessment of Cancer Therapy–Cognitive Function (FACT-Cog), version 3, a 37-item questionnaire with 4 subscales (perceived cognitive impairments, impact on quality of life, comments from others, and perceived cognitive abilities). The FACT-Cog is a reliable instrument validated in cancer populations with a Cronbach α of .89 [127]. The FACT-Cog instrument will only be administered to participants who reply “YES” to the following question at baseline: “Are you experiencing difficulties with memory, concentration, or other cognitive abilities?” As anxiety is a key determinant of quality of life in cancer survivors [23-26], the Patient-Reported Outcomes Measurement Information System–Global Health (PROMIS–Global Health) will also be administered. This validated measure contains 2 domains related to quality of life: mental health (Cronbach α=.86) and physical health (Cronbach α=.81) [128]. These measures will be administered at baseline and at weeks 4, 8, 16, and 26.

#### Treatment Expectancy

The Mao Expectancy of Treatment Effects (METE) is a 4-item instrument originally developed as the Acupuncture Expectancy Scale to measure outcome expectancy. It has demonstrated validity and reliability (Cronbach α=.82) and is correlated with patient self-reported efficacy and satisfaction [129-131]. Prior research has also demonstrated that outcome expectancy is associated with treatment response [129,132,133] and can, therefore, help inform personalized treatment decisions. The score ranges from 4 to 20, with higher scores indicating greater expectancy of benefit. This measure has been adapted for the MELODY study to assess patient expectancy of MT and CBT. The METE will be administered at baseline before receiving treatment. It will also be administered at week 8 to explore whether the expectancy changes after the treatment process.

#### Treatment Preference

As participants may have different preferences toward mental health treatment based on health beliefs or prior experiences with interventions, they will be asked at baseline whether they prefer MT or CBT or none [134]. Their preferences will also be assessed at week 8 to explore whether preferences change after their experiences with either MT or CBT.

#### Music Reward

Prior research has demonstrated variability in how people derive reward and pleasure from music, which may affect their experience with MT [135]. Therefore, the Barcelona Music Reward Questionnaire will be administered at baseline to assess the level of reward associated with music. This instrument has been validated with a Cronbach α of .92 [135].

#### Stigma of Receiving Psychological Help

In some groups and cultures, there is stigma associated with mental health needs, which may affect treatment experiences [48,49]. Therefore, the Stigma Scale for Receiving Psychological Help will be administered at baseline. This instrument has been validated (Cronbach α=.72) in different cultures to assess the stigma associated with receiving psychological health from mental health providers [136,137].

#### Covariates

Sociodemographics (eg, age, sex, race or ethnicity, and education) and other relevant clinical characteristics (eg, cancer type, stage, treatment history, and time since cancer diagnosis) will be collected at baseline. The Generalized Anxiety Disorder 7-Item Scale (GAD-7) will also be administered as a diagnostic screen for generalized anxiety disorder at baseline [138]. The use of medications prescribed for anxiety (eg, antidepressants, anxiolytics, hypnotics, and sedatives) will be tracked using weekly medication diaries at weeks 0, 8, and 26.

#### Semistructured Interviews

It may be difficult to capture the impact of MT and CBT using quantitative measures alone. Methodological experts recommend mixed methods approaches to understand patient experiences with health interventions [139-141]. Thus, qualitative method specialists will conduct 45-minute, semistructured individual interviews over the phone at week 8 (end of treatment). To reach thematic saturation from interviews, the research team will purposively sample 30 survivors in each treatment arm to be interviewed (N=60), aiming for balance across age, sex, race, ethnicity, and treatment response. Interviews will be conducted shortly after the intervention period to enhance the recall of personal experiences during therapy sessions. Interviews will be conducted using a semistructured guide that covers the following topics: (1) acceptability: treatment satisfaction, usefulness of the intervention, barriers and facilitators to session attendance, and adherence to and engagement with between-session assignments; (2) impact on anxiety symptoms and coping: perceived benefits and harms of the intervention on anxiety and comorbid symptoms, how one copes with stress and anxiety, integration of learned skills into daily life, and plans for maintaining anxiety management skills; (3) digital literacy and experience: views toward technology, comfort level with telehealth, and transfer of acquired digital skills to other aspects of daily living; and (4) unexpected experiences: unanticipated benefits, harms, or insights from engaging with the interventions. The interview guide will include flexibility in asking probing questions to enable participants to elaborate on their experiences. All the interviews will be audio-recorded and transcribed for thematic analysis.

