### Cognitive Behavioral Therapy: An Effective First-Line Treatment for Anxiety

Cognitive behavioral therapy (CBT) is an evidence-based, nonpharmacological intervention delivered by licensed mental health professionals [32,33]. The American Society of Clinical Oncology (ASCO) [27] and the National Comprehensive Cancer Network (NCCN) [34] recommend CBT for treatment of anxiety in patients with cancer. Informed by the cognitive behavioral model of anxiety, CBT focuses on the relationship between thoughts, behaviors, and emotions and how thoughts and behaviors can exacerbate or reduce anxiety [35-37]. The therapeutic components of CBT consist of psychoeducation on anxiety, relaxation techniques, cognitive restructuring, and strategies for planning activity engagement and managing realistic worries [38,39]. Meta-analyses demonstrated moderate to large effects of CBT on anxiety symptoms in patients with cancer and cancer survivors relative to control conditions, with effect sizes ranging from 0.42 to 1.10 [40-43]. CBT is widely considered an effective first-line treatment for anxiety in people affected by cancer [27,34].

Despite the established effectiveness of CBT, studies have demonstrated that 20% to 25% of CBT participants fail to complete a full treatment course [44,45] and 37% do not achieve clinically meaningful improvements in anxiety symptoms [46,47]. Furthermore, social stigma surrounding psychotherapy exists in some demographic groups and cultures, and research shows that underserved racial or ethnic groups are more likely than White patients to delay, avoid, or drop out of mental health treatments [48,49]. These challenges of CBT highlight the importance of studying other nonpharmacological treatments that are not only effective but also culturally acceptable to diverse cancer survivors.

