#### Missing Data

As the only certain way to avoid biases from missing data is to collect complete data [152], the study team will strive to minimize missing observations by using study procedures that reduce participant burden. Participants who experience difficulties completing assessments on the web will have the option to complete assessments on paper or over the telephone with the research staff. Participants with time constraints or other barriers to completing outcome assessments will be given the option to complete only the primary outcome, that is, the HADS scale. Participants who withdraw from treatments will be encouraged to continue completing the outcome assessments. Reasons for withdrawal will be recorded for those who completely withdraw from the study. Given that missing data are inevitable in a prospective study, sensitivity analyses will be performed to assess the impact on the results of adjusting for patient disease progression or death, and analytical strategies that are as robust as possible to data losses will be applied. The study team will first explore whether missingness is associated with observed variables (eg, randomization arm and baseline outcome measures) by comparing patients with complete and incomplete data. Notably, the LMMs described previously will include patients with incomplete data under the missing at random assumption. However, the exploration of the data may deem the missing at random assumption to be inappropriate. Multiple imputation and pattern mixture models are well-established methods for addressing these issues [153,154]. Sensitivity analyses will be performed to evaluate the robustness of the LMM results by refitting the models after imputing the missing week 8 and week 26 outcomes using multiple imputation.

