#### Sample Size and Power

The sample size is based on the primary hypothesis that MT is noninferior to CBT for anxiety reduction at weeks 8 and 26. Two tests will be performed to determine whether MT is noninferior to CBT at reducing HADS anxiety at weeks 8 and 26, each with a noninferiority margin of Cohen *d*=0.35 SD for both comparisons. These comparisons will be based on the LMM coefficients for the time-by-arm interaction at weeks 8 and 26; however, the power calculation is based on 2-sample *t* tests of differences between the arms in their change scores. Therefore, the power estimate is conservative, that is, in the LMM-based analysis, there will be slightly higher power than the power calculation presented below, with all other assumptions held constant. Assuming 150 participants are randomized to each arm, 15% attrition, and a 1-sided significance threshold of *P*=.025 (controlling the overall type I error at 0.05 for our 2 primary end point comparisons), there will be 80% power to find MT noninferior to CBT with respect to the HADS anxiety subscale scores at weeks 8 and 26 within a noninferiority margin of Cohen *d*=0.35 SD.

The noninferiority margin was informed by a large study that used multiple rigorous methods to empirically estimate a difference of 1.7 points as the MCID for the HADS scales [120]. In preliminary data from CBT recipients with baseline HADS anxiety subscale scores ≥8, the SD for the HADS anxiety subscale score was 4.2 at week 8 [110]. In addition, in a large acupuncture trial of cancer survivors, among 159 patients with baseline HADS anxiety subscale scores ≥8, the HADS anxiety subscale score SD was 4.0 during follow-up [155,156]. On the basis of these studies, it is assumed that the HADS anxiety subscale score SD will be approximately 4.2. Dividing the raw-score MCID of 1.7 points by 4.2 yields a standardized difference, that is, Cohen *d*=0.40. The noninferiority margin of Cohen *d*=0.35 SD is smaller than the standardized MCID (Cohen *d*=0.40) of the HADS anxiety subscale; as such, the noninferiority margin and statistical approach will find MT to be noninferior to CBT only if MT is not meaningfully worse than CBT.

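### The interviews ask about barriers to attending sessions, but the purposive sampling factors do not include attendance, so nothing secures the views of people who missed or stopped sessions

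*Protocol article*

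**What the plan says.** All places are in the protocol article.

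- **Who is interviewed.** Semistructured Interviews plans telephone interviews at week 8 with 30 survivors per arm, 60 in all, chosen purposively, "aiming for balance across age, sex, race, ethnicity, and treatment response". The list is given without an "eg" or similar opening.
- **What they are asked.** The same section makes acceptability the first of four topics. Besides satisfaction and usefulness it covers "barriers and facilitators to session attendance, and adherence to and engagement with between-session assignments".
- **How the themes are used.** Qualitative Analyses analyses the arms separately and then compares them. It relates themes to the size of the HADS anxiety change and to six example subgroup variables: sex, race, ethnicity, education, outcome expectancy and time since diagnosis. Attendance is not among them.
- **Why completion matters to this trial.** The Introduction section on CBT reports that "20% to 25% of CBT participants fail to complete a full treatment course" and that "underserved racial or ethnic groups are more likely than White patients to delay, avoid, or drop out of mental health treatments". The section on gaps in the evidence returns to non-completion when it motivates the comparison.
- **People who stop treatment.** Missing Data says: "Participants who withdraw from treatments will be encouraged to continue completing the outcome assessments". It does not mention interviews.

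**The concern.** Purposive sampling is used to make sure that the informative cases are in the sample. For barriers to attendance, the most informative cases are people who missed sessions or stopped coming. The factors in the article do not include the variable that the first interview topic is about.

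What is at stake is the qualitative comparison of MT with CBT on acceptability. If few people who stopped are interviewed, the themes on attendance come mainly from those who managed to attend. The comparison would then say little about non-completion, which the article gives as one reason for looking for an alternative to CBT. The primary noninferiority analysis and the other quantitative outcomes are not touched.

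**Working it through.** **The plan's own figure.** 30 per arm x 2 arms = 60, as stated. The number rests on thematic saturation, so there is no power formula to reproduce.

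**Does any listed factor stand in for attendance?**

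- *Treatment response.* Balancing on it brings in non-responders, some of whom may have stopped early. Response is not attendance, however: a non-responder may have attended all 7 sessions. The section does not define response. If it means change to week 8, a person lost before week 8 may have no value.
- *Race and ethnicity.* The Introduction links these to dropout, so balancing on them may help indirectly. It still fixes nothing about attendance.
- *Age and sex.* The article states no link to attendance.

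No other section of the article adds attendance, completion or withdrawal as a factor.

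**Benchmark for the CBT arm.** Inputs: q = 20% to 25% non-completion (Introduction, from other studies), 150 randomized per arm (Sample Size and Power), 30 interviewees per arm.

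- Non-completers in the arm: 150 x 0.20 = 30; 150 x 0.25 = 37.5.
- In a proportionate sample of 30: 30 x 0.20 = 6; 30 x 0.25 = 7.5.

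The article gives no MT completion rate, so there is no MT benchmark.

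**How far below the benchmark could it fall?** This needs an assumption that the documents do not supply. Let r be the chance that a non-completer is interviewed, relative to a completer. The non-completers' share of the interviews is s = qr / (qr + 1 - q), and the expected number is 30s. For example, with q = 0.20 and r = 0.5, s = 0.10 / 0.90 = 0.111 and 30s = 3.3.

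| Assumption | Expected number, q = 20% | Expected number, q = 25% |
|---|---|---|
| r = 1 (equally likely) | 6.0 | 7.5 |
| r = 0.5 | 3.3 | 4.3 |
| r = 0.25 | 1.8 | 2.3 |
| r = 0.1 | 0.7 | 1.0 |
| All of the 15% attrition are non-completers lost by week 8 and not interviewed | 1.8 | 3.5 |

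The last row uses the 15% attrition in Sample Size and Power. 150 x 0.15 = 22.5 are lost and 127.5 remain. Non-completers still present are 30 - 22.5 = 7.5 (5.9% of 127.5) or 37.5 - 22.5 = 15 (11.8%). That all losses are non-completers, and all occur by week 8, is an assumption.

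Under a random-draw binomial model with 30 interviews, the chance of two or fewer non-completers is 4.4% (q = 20%) or 1.1% (q = 25%) at r = 1, and 96% or 93% at r = 0.1. That spread shows that the documents leave the size open. The model is also only illustrative, because the team chooses whom to invite.

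**The case against.** The other side has several good arguments.

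- **People who stop are not excluded.** The sample is drawn from survivors in each arm, not from completers. Those who withdraw from treatment are encouraged to continue assessments, may answer on paper or by telephone, and may complete the HADS alone. Many could have a week 8 score and be reachable by phone. This stands.
- **Response is undefined.** A reader might infer that anyone who left before week 8 cannot be placed in the sampling scheme. The article does not support that. It does not tie response to a week 8 score, HADS is also collected at week 4, and the team could class an early leaver as a non-responder. This stands.
- **The target is saturation, not representation.** The interviews serve an exploratory hypothesis and estimate no acceptability rate. A few people who stopped may be enough to bring out their themes, and people who missed only some sessions can also describe barriers. This stands, and it is why 6 to 7.5 is a benchmark and not a requirement.
- **The article is condensed.** A fuller sampling frame may exist in a document not shown. This weakens the point but does not remove it: the article itself names the factors and the interview purpose, and the two do not match.

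**Conclusion.** The point holds as a mismatch between the interview sampling factors and the first interview topic. Nothing in the article secures interviews with people who missed or stopped sessions, and balancing on response, race and ethnicity covers them only in part.

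The only size that the documents support is the CBT benchmark of about 6 to 7.5 of 30, with no minimum in the plan. It assumes that the non-completion cited from other studies carries over to this trial's CBT arm. Any figure for the shortfall rests on assumed relative chances of being interviewed.

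A reader might go further and conclude that people who stopped will be nearly absent, that acceptability will look too favourable, or that the arm with more stopping will lose more of its critics. The first is possible but not shown. The second is a reasonable inference without a figure behind it. The third is conjecture, since no MT completion rate is given.

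This is a low-priority improvement to the exploratory qualitative component.

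**What to change.** In Semistructured Interviews:

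1. Add session attendance (completed or stopped early) to the purposive sampling factors in each arm.
2. State that people who stopped treatment are invited, and classify them by attendance where no week 8 HADS score exists.
3. Report the interviewees' attendance beside that of the whole arm, so that readers can see any gap.

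Keep 30 per arm and 60 in all. No fixed quota is needed; a quota taken from the CBT figure would have no basis for MT.

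The article reports 151 of 300 participants enrolled by January 2023, so some interviews may already have been held. The change applies to the remaining slots, while the attendance report can cover all 60. The cost is somewhat fewer completers interviewed and some extra effort to reach people who stopped.

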### Analytical Approach

#### General Description

Analyses will be conducted using the intention-to-treat principle (ie, participants will be analyzed according to their randomly assigned treatment group regardless of dropout or treatment adherence status). Given that CBT is widely recognized as a first-line therapy for anxiety, the study team opted to test the noninferiority of MT to CBT, with the goal of understanding whether MT can be an appropriate treatment option for patients who lack CBT access or do not wish to pursue CBT. To provide complementary information for treatment decision-making, the study team will also test which intervention is superior for addressing fatigue and other symptoms co-occurring with anxiety. For all specific aims, the main analytical tool will be a linear mixed-effects model (LMM) because the primary outcome (anxiety) and secondary outcomes (fatigue, depression, insomnia, pain, cognitive dysfunction, and health-related quality of life) are repeated continuous outcomes over time [142]. This statistical procedure takes into account within-subject correlations from repeated measurements in the same subjects and allows the estimation of between-group differences without necessitating the exclusion of participants with missing data. The general template of each LMM will model the outcome as a function of the treatment arm and assessment time (categorical), controlling for the randomization stratification variables (baseline anxiety medication use, preferred language, and study site) and including a subject-specific random intercept. The general LMM template will be tailored to test the specific aim hypotheses by adding interaction terms (eg, time-by-intervention) and additional covariates of interest to the model and by reparametrizing the assessment time variable to focus on specific contrasts.

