#### CBT Protocol

The CBT protocol is based on the scientific literature [32,33] and the clinical and research experience of the study team [108]. CBT therapists will include licensed social workers because they are the most commonly employed mental health providers in cancer care and, therefore, reflect the real-world practice and implementation of CBT in oncology settings [109]. Informed by the cognitive behavioral model of anxiety, CBT focuses on addressing the thoughts and behaviors that exacerbate or reduce anxiety [35-37]. The protocol consists of psychoeducation on anxiety, relaxation techniques, cognitive restructuring, and strategies for planning activity engagement and managing realistic worries [38,39]. These components target the somatic symptoms of anxiety (eg, muscle tension) as well as the thoughts (eg, “What if my next scan is bad?”) and behaviors (eg, excessive symptom monitoring) that trigger and exacerbate anxiety. Once identified, these problematic thoughts and behaviors are replaced by thoughts and behaviors that prevent and reduce anxiety. Each session will follow a consistent format that includes an overview of the session content, review of the homework exercise from the prior session, information on a new skill for managing anxiety, discussion of the upcoming homework exercise, and a plan for completing the exercise before the next session. Patients will receive a workbook with materials for each session and homework activities that promote practice of the skill learned during the session.

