#### Interventionist Training and Treatment Fidelity

All interventionists will be trained about the specific research protocol and educated on the importance of adherence to the protocol methods. The interventionists will be either English speaking or bilingual in English and Spanish. The training of study interventionists will include didactic information on anxiety in cancer survivors and review of intervention materials. Interventionists will be provided with ongoing supervision over the course of the trial. During the trial, the CBT and MT sessions will be recorded and stored on secure, encrypted MSK servers. To ensure that study therapists adhere to the treatment protocol, document treatments appropriately, and maintain fidelity to the core functions of the intervention, the session recordings for the first 2 patients seen by a therapist will be reviewed. The review of session recordings will be based on treatment fidelity checklists outlining the core intervention components. If a therapist adheres to at least 80% of the treatment fidelity checklist items, then subsequent fidelity monitoring will be reduced to 2 randomly selected session recordings per patient. Deviations from the MT or CBT protocols will be discussed with study therapists during supervision meetings, and strategies will be suggested to minimize the number of deviations. Therapists who fail to adhere to at least 80% of the treatment fidelity checklist items will be retrained. Similar treatment fidelity strategies have been successful in other MT [106] and CBT trials [108,110] of patients with cancer conducted by the study team.

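### The stated model and power calculation treat participants who share a therapist as independent; if outcomes cluster by therapist, the noninferiority test is too lenient and the 80% power is optimistic

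*Protocol article*

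**What the plan says.** **Delivery.** Under MT Protocol, music therapy is given by board-certified music therapists. Under CBT Protocol, "CBT therapists will include licensed social workers". Therapists therefore appear to be nested within arm. Interventionist Training and Treatment Fidelity states that "the session recordings for the first 2 patients seen by a therapist will be reviewed", and that monitoring of later patients is lighter once a therapist reaches 80% on the checklist. A therapist is thus expected to go on beyond two patients. The article gives no therapist numbers and no caseload.

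**Model.** Under General Description, the LMM has fixed effects for arm, categorical time, anxiety medication, language and site, and one random effect, a participant intercept. The dependence it is said to handle is within participants: "This statistical procedure takes into account within-subject correlations from repeated measurements in the same subjects". No therapist term is named.

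**Power.** Under Sample Size and Power: "Assuming 150 participants are randomized to each arm, 15% attrition, and a 1-sided significance threshold of *P*=.025", "there will be 80% power to find MT noninferior to CBT", "each with a noninferiority margin of Cohen *d*=0.35 SD for both comparisons". The calculation is a two-sample t test on change scores with no ICC or design effect. The section adds "Therefore, the power estimate is conservative", and explains this as a comparison of the t test with the LMM when everything else is kept the same.

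**The concern.** Participants treated by the same therapist may have more similar outcomes after treatment than participants treated by different therapists. With therapists nested in arm, that shared component does not cancel from the arm difference. It adds variance that a participant intercept cannot represent. Site and language effects do not remove therapist differences within a site.

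In a noninferiority test an understated standard error favours success, because the confidence limit falls inside the margin too easily. The Aim 1 section states that testing each comparison at .025 holds the overall error at .05, and Sample Size and Power states that MT will be called noninferior only when it is not meaningfully worse. Both statements need a valid standard error. Without a therapist term, variation among the particular therapists employed can also be mistaken for a difference, or an absence of difference, between the two treatments.

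**Working it through.** **Inputs from the article (Sample Size and Power).** 150 randomized per arm, 15% attrition, one-sided 0.025, margin 0.35 SD. The article also says "it is assumed that the HADS anxiety subscale score SD will be approximately 4.2", which makes the margin 0.35 × 4.2 = 1.47 points; the SD cancels on the standardized scale. Evaluable per arm: n = 150 × 0.85 = 127.5.

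**Assumed, because the article does not give them.** True difference 0; k = 6 to 15 therapists per arm with equal caseloads; therapist ICC (ρ) of 0.01 to 0.05 for the change in HADS anxiety, the same in both arms.

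**Step 1: reproduce the stated power.** Power = Φ(0.35 × √(n/2) − 1.96) = Φ(0.35 × √63.75 − 1.96) = Φ(2.794 − 1.96) = Φ(0.834) = 79.8%. The noncentral t gives 79.5%. The stated 80% is therefore correct under independence.

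**Step 2: allow for clustering.**
- Caseload m = 127.5/k
- Design effect DE = 1 + (m − 1)ρ
- Actual one-sided error if clustering is ignored = 1 − Φ(1.96/√DE)
- Power if clustering is analysed correctly = Φ(2.794/√DE − 1.96)

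| k per arm | m | ρ | DE | √DE | One-sided error if ignored | Power, normal | Power, t with 2(k − 1) df |
|---|---|---|---|---|---|---|---|
| any | – | 0 | 1 | 1 | 0.025 | 80% | see fix |
| 15 | 8.5 | 0.01 | 1 + 7.5 × 0.01 = 1.075 | 1.037 | 0.029 | 77% | 74% |
| 10 | 12.75 | 0.02 | 1 + 11.75 × 0.02 = 1.235 | 1.111 | 0.039 | 71% | 66% |
| 6 | 21.25 | 0.05 | 1 + 20.25 × 0.05 = 2.0125 | 1.419 | 0.084 | 50% | 43% |

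The middle row in full: error = 1 − Φ(1.96/1.111) = 1 − Φ(1.764) = 0.039; power = Φ(2.794/1.111 − 1.96) = Φ(0.555) = 71%.

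**Step 3: consequences.** A correct interval would be about 4% to 42% wider (√DE 1.037 to 1.419). In the middle row, two tests at 0.039 bound the overall error at 2 × 0.039 = 0.078, against the stated .05. Unequal caseloads would raise the design effect further.

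**Step 4: could the LMM's efficiency gain make up for it?** The variance reduction needed is 1 − 1/DE: 7%, 19% and 50% in the three rows. The article claims only slightly higher power for the LMM than for the t test.

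**The case against.** **The size is unknown.** Every figure above with clustering rests on two assumed parameters, and nothing in the article places the trial within the range. A reader might infer that the interval is too narrow as a matter of fact, or that each therapist treats many participants. The article supports neither. It shows only a caseload of more than two, and at an ICC of 0 the 80% and the 0.025 both hold. Training, continuing supervision, fidelity checklists with an 80% threshold and retraining also work to limit differences between therapists. This stands: the claim is conditional. These measures do not show that the ICC is zero, and any positive ICC moves error and power in the unfavourable direction.

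**The conservatism sentence.** A reader might infer that it is false. It is not. It compares the t test with the LMM under the same assumptions, and independence between participants is one of them. For that reason it also cannot support 80% as a lower bound on true power. It needs a qualifier, not deletion.

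**A condensed article.** The full protocol and analysis plan are not shown, the model is called a template, and a clustering analysis could be specified there. This stands in part: it cannot be said that the trial will ignore therapists. But the article does state the random effect and the basis of the power calculation. The tailoring it describes covers interactions, covariates and the coding of time, not the random effects.

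**Reporting guideline.** A reader might infer that the guideline for nonpharmacological trials cited under Study Design settles the matter. The article does not say what that guideline requires on providers, so nothing here relies on it.

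**Conclusion.** The concern holds in conditional form. The stated model and power calculation assume independence between participants who share a therapist, in a design where therapists appear nested within arm and each sees several participants. If the therapist ICC is above 0, the standard error of the primary contrast is understated, noninferiority is declared too easily and the 80% power is optimistic. Under the assumed 6 to 15 therapists per arm and ICC of 0.01 to 0.05, the one-sided error per test is about 0.029 to 0.084 and power about 77% to 50%. The lower end is minor and the upper end serious. The article does not allow a choice between them, which is why the analysis should cover the possibility.

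**What to change.** 1. Add to the primary LMM a therapist random effect, nested in arm, that acts on the post-baseline visits. Baseline is assessed before randomization, so no therapist can have influenced it. A therapist intercept held constant over all visits would largely cancel from the change-from-baseline contrasts and protect nothing.
2. Use small-sample degrees of freedom, for example Kenward-Roger. If therapists are too few to estimate the variance component, use an equivalent cluster-robust analysis with a small-sample correction.
3. Report the number of therapists per arm, their caseloads and the estimated ICC.
4. State that the 80% power assumes no therapist clustering, and give power over a range such as ICC 0.01 to 0.05 with the actual therapist numbers.
5. Keep the conservatism sentence, but say that it compares the t test with the LMM only.

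**Cost.** No new outcome data are needed, and fidelity review is already organised by therapist, so therapist identity should be available. Intervals will be somewhat wider and the power figure less favourable. If degrees of freedom are taken wholly at the therapist level, 2(k − 1), power falls even at an ICC of 0: from 80% to about 77%, 75% and 71% with 15, 10 and 6 therapists per arm.
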